## Abstract

**Background:**

Adherence to evidence-based cardiovascular risk factor targets in patients with type 2 diabetes and microalbuminuria has shown long-term reduction in mortality and morbidity. Strategies to achieve such adherence have been delivered at individual patient level and are not cost-effective. Health care professional-level intervention has the potential to promote better adherence at lower cost.

**Objective:**

The aim of this study was to assess the effectiveness of a multifactorial technology-driven intervention comprising health care professional training, a software prompt installed on practice systems, clinician email support, and enhanced performance and feedback reporting.

**Methods:**

A cluster randomized trial will be performed where the primary outcome is the proportion of eligible patients meeting tight cardiovascular risk factor targets, including systolic and diastolic blood pressure (BP; BP<130/80 mm Hg) and total cholesterol (TC; TC<3.5 mmol/L) at 24 months. Secondary outcomes include proportion of patients with glycated hemoglobin (HbA_1c_) <58 mmol/mol (7.5%), change in medication prescribing, changes in microalbuminuria and renal function (estimated glomerular filtration rate, eGFR), incidence of major adverse CV events and mortality, and coding accuracy. Cost-effectiveness of the intervention will also be assessed.

**Results:**

Among 2721 eligible patients, mean age was 62.9 (SD 10.0) years, and duration of diabetes was 10.46 (SD 7.22) years. Mean HbA_1c_ was 59.3 (SD 17.4) mmol/mol; mean systolic and diastolic BP (mm Hg) were 134.3 (SD 14.6) and 76.1 (SD 9.5) mm Hg, respectively; and mean TC was 4.1 (SD 0.98) mmol/L. Overall, 131 out of 2721 (4.81%) patients achieved all 3 “tight” cardiovascular risk factor targets. Cardiovascular risk factor burden increased two-fold in those with eGFR<60 mL/min/1.73 m^2^ compared with those with eGFR≥60 mL/min/1.73 m^2^. Prevalence of microalbuminuria was 22.76%. In total, 1076 out of 2721 (39.54%) patients were coded for microalbuminuria or proteinuria on their primary care medical record.

**Conclusions:**

The general practitioner prompt study is the largest UK primary care-based, technology-driven, randomized controlled trial to support intensive intervention in high-risk group of multiethnic individuals with type 2 diabetes and microalbuminuria. This paper provides contemporary estimates for prevalent cardiovascular disease and adherence to evidence-based cardiovascular risk factor targets at baseline in a population with type 2 diabetes and microalbuminuria. The main trial results, including cost-effectiveness data, will be submitted for publication in 2018.

**Trial Registration:**

International Standard Randomized Controlled Trial Number ISRCTN14918517; http://www.isrctn.com/ISRCTN14918517 (Archived by WebCite at http://www.webcitation.org/6zqm53wNA)

**Registered Report Identifier:**

RR1-10.2196/9588

## Introduction

### Type 2 Diabetes and Microalbuminuria

Microalbuminuria (MA) in patients with type 2 diabetes (T2DM) is associated with a significantly increased risk of cardiovascular (CV) mortality and related morbidity [1]. Current evidence advocates targeted, tight, multiple risk factor control to reduce CV risk [2]. Recent audit data suggest that despite current guidance, over 80% of patients with MA and T2DM do not meet all treatment targets for blood pressure (BP), total cholesterol (TC), and glycated hemoglobin (HbA_1c_) [3].

### Evidence for Tighter Cardiovascular Risk Factor Control

Previous studies have demonstrated the effectiveness of patient-level interventions using tighter treatment targets [4,5] including group patient education [3,6], showing long-term beneficial microvascular and macrovascular benefits in addition to reduced mortality.

Strategies to improve quality of care in diabetes, including health care professional (HCP) education, providing financial incentives, professional reminders, and audit and feedback, have generally reported improvements in care, albeit with modest reductions in HbA_1c_ [7]. Due to differences in interventions, outcome measures, and study populations, it is difficult to compare data on effectiveness between clinician- and patient-focused interventions [8].

Although there is evidence to suggest that patient-level interventions to manage CV disease (CVD) are cost-effective [9], questions loom over the ability to implement them with limited resources available in primary care settings. Simple prompts integrated into existing information technology (IT) systems to identify patients during routine consultation, in combination with education for clinicians, may serve as an “aide-mémoire” and provide an opportunity to improve standards of care at low cost [10-12]. More specifically, it has been shown to improve adherence to medication in studies targeting a reduction in CVD risk in people with T2DM [13,14]. The provision of patient “reminders” and audit and feedback are facilitated through existing practice IT systems [15]. This highlights opportunities for intervention in patients at the time of clinical encounter [16] and is effective in improving HCP behavior to achieve patient risk factor targets [15].

### The General Practitioner-Prompt study

The general practitioner (GP) prompt study was designed to test the hypothesis that a multifaceted, multifactorial intervention in patients with T2DM and MA aimed at primary care HCPs aided with an electronic “Prompt” would result in a selective, intensive, and targeted intervention of CV risk factors in these high-risk individuals and an increase in the proportion meeting tight multiple CV risk factor targets [2].

## Methods

### Study Design

This study is a pragmatic cluster randomized controlled trial (RCT). Ethics approval was granted by the National Research Ethics Committee: North West Lancaster on March 16, 2015 (ref: 166517).

The rationale for randomizing at the cluster level was that the intervention was implemented across all eligible patients, and treatment decisions regarding individual patients remained the responsibility of HCPs at each practice [17,18].

The duration of this trial is 24 months. The installation of the prompt took place on November 1, 2015. Patients registered with control practices continued to receive usual care in line with current best practice guidelines [2].

This paper reports the trial design and baseline biomedical characteristics, including CV risk factor burden and medication management data in this study population.

### Setting

Eligible practices (using EMIS Web or SystmOne IT systems and a list size of >6000 patients) within the recruitment area of Leicester City and Leicestershire County were sent an invitation summarizing the study design and protocol. Staff members who expressed an interest were offered a meeting with a member of the study team to clarify any queries regarding the study. Informed consent and information governance approval was sought among eligible practices willing to participate and documented from a senior GP partner or practice manager and Caldecott Guardian. Practices were then randomized by a member of the Leicester Clinical Trial Unit (not involved with the study) to the intervention or control arm. A 1:1 randomization was stratified based on size of diabetes register (small practices <600 patients, large practices >600 patients).

### Patient Inclusion Criteria

Patient-level data were extracted for individuals aged between 17 and 76 years with a Read code for T2DM and MA or overt proteinuria on their clinical record, or individuals with T2DM and albumin-creatinine ratio (ACR)>2.5 in males and >3.5 in females on 2 consecutive occasions of >90 days and <180 days apart, having excluded a urinary tract infection [2].

### Patient Exclusion Criteria

Data were not extracted if patients fulfilling the inclusion criteria were pregnant, terminally ill, or excluded from the Pay for Performance—Quality and Outcomes Framework (QOF; whole domain diabetes) [19].

### Intervention

The multifactorial intervention uses an IT software prompt and care template to alert HCPs to eligible patients attending a routine consultation (Multimedia Appendices 1 and 2). The software prompt and care template was developed by an external software company, with refinement informed by feedback from HCPs during an initial focus group. The prompt and care template is triggered when patients with T2DM and MA as well as BP, TC, or HbA_1c_ above target attend a consultation. The HCP is alerted to risk factors that are above target and displays the patient’s last 12-month values for each risk factor. The prompt also allows the clinician to access an evidence-based treatment algorithm recommending specific therapies that can be followed to achieve tight-targeted risk factor control (Multimedia Appendix 3). If sufficient control cannot be achieved, a link to a study email address is available for HCPs to request further individualized advice. This advice is provided within 1 week via email by a study clinician. An existing patient education leaflet emphasizing the importance of treatment adherence will also be available for eligible patients. Practice staff attended training before the prompt was installed and are provided with ongoing support and feedback during the study period (Multimedia Appendix 4).

### Primary and Secondary Outcomes

The primary outcome is the proportion (%) of eligible patients meeting both of the following CV risk factor targets: BP<130/80 mm Hg and TC<3.5 mmol/L. These outcomes were selected as they are current recommended care processes and clinical outcomes of care for the management of individuals with T2DM and MA [20,2].

Secondary outcomes include the following: incidence of CV events and all-cause mortality, smoking status glycemic control assessed by HbA_1c_, progression in MA assessed by change in ACR, kidney function measured by change in estimated *glomerular filtration rate* (e*GFR*), changes in T2DM, BP, and cholesterol-lowering medication prescribing, including contraindications and adverse reactions. Data extracted relate to blood samples that are previously collected as part of routine care and analyzed in accordance with relevant regulations and standard operating procedures.

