### Analysis Plan

We are using a cluster randomized design with repeated measurements, and therefore, there is a high likelihood that biomedical characteristics may correlate within a cluster. We will perform linear and logistic multilevel regression analyses to study the effects of the intervention with cluster as the random effect, adjusted for the baseline value of the outcome both at practice and individual levels, using the missing indicator method for “missing” baseline data. Data will be analyzed as intention-to-treat, and differences in outcomes measures between the intervention and control groups will be calculated with 95% CI. It is also likely that not all individuals from the control group will have had regular appointments with their GP; hence, we will perform a sensitivity analysis to compare “attenders” at similar time points in the intervention versus control group.

For presentation of baseline data, we will use Pearson chi-square to analyze differences in proportions between intervention and control groups. Independent samples *t* tests will be used to analyze differences in continuous variables between study groups. Statistical analyses of the baseline data and all future analysis will be carried out using STATA version 14 [26].

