## Results

Baseline data have been extracted from 22 practices (12 controls and 10 interventions; Figure 1) with a reference date of October 30th, 2015. The total number of patients registered at participating practices is 232,639. There are 2721 patients with T2DM meeting the study MA criteria and eligible for the study. Of these 2721, 1067 patients (39.5%; 95% CI 37.7-41.4) had a code for MA or proteinuria in their electronic medical notes.

Biomedical characteristics, current risk factor control, medical history, and current drug prescriptions of the study population are shown in Tables 1-3. The mean age of patients is 62.9 (SD 10.0) years. There are no significant differences in number of male or female patients, and the study population, in keeping with local demographics, is predominantly of South Asian ethnicity (1136/1838 patients, 61.77%). The mean duration of T2DM is 10.5 (SD 7.2) years. Out of 2721 participants, 415 (15.25%) and 739 (27.16%) patients are current smokers and ex-smokers, respectively. Out of 2721 patients, 536 (19.70%) have chronic kidney disease stage 3.

The mean HbA_1c_ is 59.3 (SD 17.4) mmol/mol , mean systolic and diastolic BP (mm Hg) is 134.3 (SD 14.6) and 76.1 (SD 9.5) mm Hg, respectively, and mean TC is 4.1 (SD 0.98) mmol/L. Out of 2721 patients, 630 (23.15%) had achieved a tight BP target of <130/80 mm Hg and 707 patients (25.98%) had achieved a tight TC target of <3.5 mmol/L. Overall, 131 out of 2721 (4.81%) patients achieved all 3 “tight” CV risk factor targets. CV risk factor burden assessed by the prevalence of coronary heart disease, cerebrovascular disease, and peripheral vascular disease increased two-fold in those with eGFR<60 mL/min/1.73 m^2^ compared with those with eGFR≥60 mL/min/1.73 m^2^. Overall, 1076 out of 2721 (39.46%) individuals had a code for MA or proteinuria on their primary care medical record. Out of 2721 patients, 2064 (75.85%) were prescribed a nephroprotective agent, such as an angiotensin-converting enzyme inhibitor or an angiotensin receptor blocker drug, whereas 2070 patients (76.07%) were prescribed a cholesterol-lowering medication, that is, statin therapy.

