**Figure 1 figure1:**
[figure not shown]
Recruitment flowchart. T2DM: type 2 diabetes; MA: microalbuminuria.

**Table 1 table1:** Biomedical characteristics of eligible study patients.

Characteristics		Control (N=1299)	Intervention (N=1422)	Total (N=2721)	*P* value
Age in years, mean (SD)		62.8 (10.1)	62.9 (9.9)	62.9 (10.0)	.63

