**Medical history, n (%)**					
	Myocardial infarction	97 (7.47)	89 (6.26)	186 (6.84)	.21
	Acute coronary syndrome	51 (3.93)	57 (4.01)	108 (3.97)	.91
	Angina	120 (9.24)	132 (9.28)	252 (9.26)	.97
	Ischemic heart disease	249 (19.17)	264 (18.57)	513 (18.85)	.68
	Transient ischemic attack	66 (55.08)	35 (2.46)	101 (3.71)	<.001
	Stroke	46 (3.54)	55 (3.87)	101 (3.71)	.65
	Peripheral vascular disease	48 (3.70)	34 (2.39)	82 (3.01)	.047
	Revascularization procedure	92 (7.08)	40 (2.81)	132 (4.85)	<.001
	Bypass graft	47 (3.62)	53 (3.73)	100 (3.68)	.88
**Number of study risk factors controlled, n (%)^g^**					**.21**
	0	336 (25.87)	337 (23.70)	673 (24.73)	
	1	579 (44.57)	680 (47.82)	1259 (46.27)	
	2	309 (23.79)	336 (23.63)	645 (23.70)	
	3	70 (5.39)	61 (4.29)	131 (4.81)	
MA^h^/proteinuria code, n (%)		410 (31.56)	666 (46.84)	1076 (39.54)	<.001

^a^T2DM: type 2 diabetes.

^b^HbA_1c_: glycated hemoglobin.

^c^BP: blood pressure.

^d^eGFR: estimated glomerular filtration rate.

^e^IQR: interquartile range.

^f^CKD: chronic kidney disease.

^g^HbA_1c_ <7.5% (58.5 mmol/mol), total cholesterol <3.5 mmol/L, BP <130/80 mm Hg.

^h^MA: microalbuminuria.

**Table 2 table2:** Vascular burden between patient groups categorized by chronic kidney disease stages.

Disease characteristic		Patients with MA^a^ and eGFR^b^ <60			Patients with MA and eGFR>60		
		Control (N=280)	Intervention (N=258)	Total (N=538)	Control (N=1019)	Intervention (N=1164)	Total (N=2183)

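### The one named covariate, the baseline value of the outcome, does nothing for all-cause mortality and is undefined for incident CV events, so the mortality comparison has no individual-level adjustment

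*Protocol article*

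**What the plan says.** Under Primary and Secondary Outcomes, the protocol article names "incidence of CV events and all-cause mortality" among the secondary outcomes. The Abstract speaks of major adverse CV events and mortality.

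The Analysis Plan sets out "linear and logistic multilevel regression analyses to study the effects of the intervention with cluster as the random effect". These models are "adjusted for the baseline value of the outcome both at practice and individual levels", "using the missing indicator method for “missing” baseline data". No other covariate is named, and no outcome is exempted from the rule.

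On allocation, the Setting section says: "A 1:1 randomization was stratified based on size of diabetes register". The Results section reports baseline data from "22 practices (12 controls and 10 interventions"). Table 1 gives 1299 control and 1422 intervention patients, with baseline vascular history by arm, including the row "Revascularization procedure".

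**The concern.** Adjusting for the baseline value suits blood pressure, cholesterol, HbA1c, ACR and eGFR, which are measured at both ends of follow-up. It does not suit death. Every patient in the baseline extract is alive, so the covariate has the same value for everyone and drops out of the model. Its practice mean is constant too, and the article describes no extraction of earlier practice death rates. The missing indicator method does not help, because the value does not exist; it is not merely unrecorded. For an incident CV event, the reader must guess whether prior history is meant.

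Two things are at stake. The first is efficiency: age, prior vascular disease and eGFR are likely to predict death and CV events, and leaving them out gives up information. In a logistic model the gain from including them shows mainly as power. The second is protection against chance imbalance. With 22 randomized practices and register size as the only stratifier, vascular history is not balanced by design, and Table 1 shows that some of it did not come out balanced.

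**Working it through.** **Inputs.** Counts are from Table 1, and from the column headings of Table 2 for eGFR below 60. Denominators are 1299 control and 1422 intervention. The Table 1 percentage for control TIA is printed as 55.08, but 66/1299 = 5.08%, so it is a misprint.

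**Step 1: reproduce the printed P values.** Pearson chi-square without continuity correction gives 0.0003 for TIA (printed <.001), <0.0001 for revascularization (printed <.001) and 0.0469 for peripheral vascular disease (printed .047). All three agree.

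**Step 2: the baseline picture.**

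| History | Control | Intervention |
|---|---|---|
| Revascularization | 92 (7.08%) | 40 (2.81%) |
| TIA | 66 (5.08%) | 35 (2.46%) |
| Peripheral vascular disease | 48 (3.70%) | 34 (2.39%) |
| eGFR below 60 | 280 (21.6%) | 258 (18.1%) |
| MI | 97 (7.47%) | 89 (6.26%) |
| Ischemic heart disease | 249 (19.17%) | 264 (18.57%) |
| Angina | 120 (9.24%) | 132 (9.28%) |
| Acute coronary syndrome | 51 (3.93%) | 57 (4.01%) |
| Stroke | 46 (3.54%) | 55 (3.87%) |
| Bypass graft | 47 (3.62%) | 53 (3.73%) |

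Three of the nine vascular rows show a clear excess in control. MI leans the same way (P=.21), and the other five are level. Mean age is also level (62.8 v 62.9 years), so adjusting for age would serve efficiency, not balance.

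**Step 3: allow for clustering.** Each arm's variance is multiplied by 1 + ((CV² + 1)m − 1) × ICC. CV = 1.11 is the cluster-size variation in Sample Size Considerations, and m = 1299/12 = 108.25 or 1422/10 = 142.2. Using the ICC of .05 stated there for the primary outcome (borrowed here), the factors are:

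- control: 1 + (2.2321 × 108.25 − 1) × 0.05 = 13.0
- intervention: 1 + (2.2321 × 142.2 − 1) × 0.05 = 16.8

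The P values become 0.17 (revascularization), 0.34 (TIA) and 0.60 (peripheral vascular disease). At an assumed ICC of .01 they are 0.007, 0.06 and 0.31.

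**Step 4: size of a possible tilt.** Suppose a history with prevalence p multiplies risk by r, and the intervention does nothing. The unadjusted intervention/control risk ratio is then [1 + (r − 1)p_int] / [1 + (r − 1)p_ctrl]. The documents give neither event rates nor r, so r = 2 to 3 is an assumption.

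- *Composite prior disease* (ischemic heart disease + TIA + stroke + peripheral vascular disease; other coronary codes assumed to fall within ischemic heart disease; no overlap between the four). Control: 249 + 66 + 46 + 48 = 409, or 31.5%. Intervention: 264 + 35 + 55 + 34 = 388, or 27.3%. Ratio at r = 2: 1.273/1.315 = 0.968. At r = 3: 1.546/1.630 = 0.948. That is 3-5%.
- *Only the three imbalanced codes, no overlap.* Control: 92 + 66 + 48 = 206, or 15.86%. Intervention: 40 + 35 + 34 = 109, or 7.67%. Ratio at r = 2: 1.0767/1.1586 = 0.929. At r = 3: 0.875. That is 7-12%. If the codes are instead treated as independent with multiplying risks, the ratios are 0.924 and 0.860.
- *Revascularization alone.* 1.0281/1.0708 = 0.960 and 1.0562/1.1416 = 0.925.
- *eGFR below 60 alone.* 0.972 and 0.952. This should not simply be combined with the figures above, because Table 2 shows vascular disease concentrated in that group.

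**The case against.** The strongest reply is that this is a journal article. Its modelling sentence is general, comes after a reference to repeated measurements, and does not claim to list every covariate. An analysis plan that is not shown may name others. That would answer a complaint about missing detail. But the article does state a rule, without exception, and the rule cannot work for an outcome the article itself lists.

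For CV events the reply has more force. Prior CV history is extracted for each patient and is a natural reading of baseline value. On that reading those events would be adjusted, and only mortality is certainly uncovered.

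A reader might go further and infer that the control arm is sicker overall and that the event comparisons are biased towards the intervention. The documents do not support that, for four reasons:

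- Five of the nine history rows, including ischemic heart disease (the commonest) and stroke, are balanced.
- After clustering is allowed for at the stated ICC, the differences are compatible with chance, so this is not a design bias.
- The revascularization row is doubtful. Intervention has 40 such codes but 53 bypass grafts, while control has 92 and 47. The Limitations section warns that accuracy depends on local coding, and MA/proteinuria coding itself differs by arm (31.56% v 46.84%). Part of the gap may be recording, which adjustment would not remove.
- Recorded Asian ethnicity (73.20% intervention v 52.02% control) and statin use (78.13% v 73.83%) also differ, with effects on risk that the documents do not quantify.

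Compatibility with chance does not settle the matter, though. A realised imbalance in a prognostic factor moves an unadjusted estimate whatever its P value.

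**Conclusion.** The point holds for mortality, where the stated covariate is constant and leaves no individual-level adjustment. For incident CV events it holds as an undefined term. Comparisons made without prognostic covariates are less efficient and are exposed to a chance imbalance that may favour the intervention. The size is about 3-5% for a composite prior-disease history, and 7-12% if only the three imbalanced codes are counted without overlap. Both ranges assume risk ratios of 2 to 3 that the documents do not give. The net direction is not established. The primary outcome has a baseline value and is not affected. The change is worth making, but nothing in the trial's main conclusion depends on it.

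**What to change.** For all-cause mortality and CV events, replace the baseline-value rule with adjustment for baseline age, sex, any prior coronary, cerebrovascular or peripheral vascular disease, and eGFR, keeping practice as a random effect. A composite history also depends less on any single doubtful code than the separate rows do. State how an incident CV event is defined in relation to prior history. Settle both before the 24-month outcomes are analysed.

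The cost is a sentence or two of analysis wording, since all these variables are already in the baseline extract. The downside is a few extra model parameters, which matters only if events are few.
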